**Epidural Catheter**

Ease of insertion and complications during catheter insertion and removal- Bleeding/ difficult or impossible at the hands of experts/ hematoma/ catheter break/ accidental removal/ blockage/ other.

**Analgesia, Sedation, Fever**

VAS and RASS scores are charted four^th^ hourly in the ICU- a daily mean score will be collected from the daily data sheets of the patients.

Any temperature > 101 F will be noted as the number of episodes per day.

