**The research question**

Aim To compare the TFDi (primary endpoint), ventilator parameters, subjective comfort, rate of intubation, length of mechanical ventilation, length of ICU stay, and mortality of moderate to severe COVID 19 patients on noninvasive ventilation (NIV), with and without epidural morphine.

*Objectives*

To compare-

Thickening Fraction index of diaphragm TFdi, surrogate for the respiratory drive (primary outcome measure)

P0.1, mechanical ventilation (MV), respiratory rate (RR), Tidal volume (Vt), subjective comfort, the dose of sedatives needed, Visual Assessment of Pain (VAS), Richmond Agitation and Sedation Scores (RASS), time to intubation, length of mechanical ventilation, the incidence of VAP, incidence of sepsis, COVID 19 markers, length of stay in ICU, length of stay in hospital and mortality between the two groups.

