**The interventions**

A baseline assessment of all outcome measures as appropriate will be made. Normal body temperature, RASS of -1 or 0, and VAS < 4 will be ensured by administering Midazolam ( titrated to effect) or Paracetamol as warranted.

All patients will be turned lateral or sitting position, and an injection of LA be given at L2-3 or L3-4 space. An epidural catheter will be inserted under all asepsis and fixed to the skin in the intervention group. It will be fixed firmly with antimicrobial incise drapes covering at least the lower one-third of the back. For patients who appear fidgety, catheter tunneling may also be used.

The control group will have a sham catheter fixed precisely like the intervention group but not entering the epidural space. The fixation and dressing will be similar to the intervention group.

The intervention group will be administered Injection Morphine Sulphate once every 18-24 hours into the epidural space. The doses will be escalated daily (5-10mg), titrated to the effect: escalation limited by hypoventilation resulting in respiratory acidosis (pH <7.2).

The intervention will continue for a minimum of 2 doses and a maximum of 4 doses (96 hours) of morphine. It will be stopped at 120 hours, or if: the epidural catheter gets dislodged before the second dose, the patient is weaned off noninvasive ventilation to high flow mask for a continuous period of 12 hours or requires endotracheal intubation.

The patient will be followed up till death or 28 days after ICU discharge.

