**Outcome assessment**

*Outcome measures*

TFdi, p0.1, MV, RR, Vt (average of 3 readings, ^eighth^ hourly )

Arterial blood gas and associated values-Pa o2, PaCO2, pH, HCO3, p/F ratio (at least once a day)

Spo2, Fio2, ROX index, Subjective comfort and dyspnea scores – 8^th^ Hourly

VAS, RASS, Weaning (hours off NIV on high flow mask or face mask)- (mean values over 24 hours)

Intubation- Yes/ No: Days after randomization

Length of stay in ICU

Outcome at 28 days of admission

Incidence of excessive respiratory depression (PaCO2> 45 and pH < 7.2)

Incidence of difficult/ failed epidural insertion, catheter pullouts, and complications such as bleeding/ infection/ hematoma will be documented.

Timing of outcome assessment- - Every 8^th^-hour assessment / daily / one time as detailed above

Blinding- The assessor, patient, nurses, physicians, and treating team will be blind to group allocation. One member of the team not involved in research will administer the drug.

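### Keeping only a daily mean of four-hourly RASS lets a short or moderate episode of deep sedation disappear from the trial data

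*Protocol*

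**What the plan says.** RASS is one of the between-group comparisons in the objectives (Protocol, The research question: "Richmond Agitation and Sedation Scores (RASS").

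Two places fix how it is kept. The outcome list gives "VAS, RASS, Weaning (hours off NIV on high flow mask or face mask)- (mean values over 24 hours". The section Analgesia, Sedation, Fever says that "VAS and RASS scores are charted four"-hourly in the ICU and that "a daily mean score will be collected from the daily data sheets of the patients". The two agree, so the daily mean is a stated rule.

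The only RASS level that the protocol names is at baseline: "RASS of -1 or 0, and VAS < 4 will be ensured" (The interventions). Morphine is then given "once every 18-24 hours into the epidural space", with daily escalation.

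No section asks for the lowest RASS of the day, a count of deep readings, or an over-sedation event. Fever, in the same section as RASS, is counted as episodes per day.

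**The concern.** A mean suits a quantity whose highs and lows may fairly offset each other. RASS is not one: negative scores are sedation, positive scores are agitation, and the steps are ordinal. Opposite signs can cancel. Even without positive readings, a short trough is diluted by ordinary readings on the same day. With about one morphine dose per averaging day, a trough after the dose is pooled with the rest of that day.

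What is at stake is whether the arms can be compared for over-sedation in a trial of an escalating opioid, where midazolam and dexmedetomidine may also be given. Two arms could have similar daily means and differ in how often patients were deeply sedated, and the extracted data would not show it.

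**Working it through.** The protocol states no figure for this point, so there is none to reproduce. The check asks which six-reading days give a mean between -1 and 0.

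**Inputs**
- Readings per day: 24 / 4 = 6 (Analgesia, Sedation, Fever).
- Reference band: -1 to 0, the baseline state (The interventions).
- Assumption: RASS takes integers from -5 to +4. The protocol does not define the scale. *Deep* is tried both as -3 or lower and as -4 or lower.

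**Formula:** daily mean = (sum of the six readings) / 6. The mean is in the band when the sum lies from -6 to 0.

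| Six readings | Sum | Mean | In band? | Lowest | Below -1 | Above 0 |
|---|---|---|---|---|---|---|
| -4, 0, 0, 0, 0, 0 | -4 | -0.67 | yes | -4 | 1 | 0 |
| -3, -3, 0, 0, 0, 0 | -6 | -1.00 | yes | -3 | 2 | 0 |
| -4, -4, +1, +1, 0, 0 | -6 | -1.00 | yes | -4 | 2 | 2 |
| -3, -3, -3, +1, +1, +1 | -6 | -1.00 | yes | -3 | 3 | 3 |
| -1 six times | -6 | -1.00 | yes | -1 | 0 | 0 |
| -4, -4, 0, 0, 0, 0 | -8 | -1.33 | no | -4 | 2 | 0 |
| -4, then -1 five times | -9 | -1.50 | no | -4 | 1 | 0 |

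Four different days share a mean of -1.00. The last three columns tell them apart.

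**How many deep readings can an in-band mean hide?** Let k readings sit at the deep threshold t and the other 6 - k at the highest score h seen that day. The sum must be at least -6, so k·t + (6 - k)·h ≥ -6.

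- t = -3: h = 0 gives 3k ≤ 6, so k ≤ 2; h = +1 gives 4k ≤ 12, so k ≤ 3; h = +4 gives 7k ≤ 30, so k ≤ 4.
- t = -4: h = 0 gives 4k ≤ 6, so k ≤ 1; h = +1 gives 5k ≤ 12, so k ≤ 2; h = +4 gives 8k ≤ 30, so k ≤ 3.

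Enumerating all six-reading days gives the same maxima. If each reading stands for its four-hour interval, two readings of -3 represent about 2 × 4 = 8 hours.

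**What the other records would catch**
- "Incidence of excessive respiratory depression (PaCO2> 45 and pH < 7.2" (Outcome assessment) measures ventilation, not depth of sedation, and blood gases are required only "at least once a day".
- A Glasgow coma score below 12 is a criterion for intubation, and neurologic dysfunction is one recorded cause of conversion to invasive ventilation. Both reach the data through intubation.
- Sedative doses are noted at each diaphragm ultrasound. These show what was given, not the resulting depth.

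A trough that leads neither to intubation nor to a blood gas meeting both limits leaves no mark in these records.

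**The case against.** The strongest reply is that little is really lost. Sustained deep sedation moves the mean: six readings of -3 give -3.00, and even two of -4 with four of 0 give -1.33, outside the band. The more dramatic mixtures need deep sedation and agitation on one day in a patient on NIV, and prolonged deep sedation would probably surface through the coma-score criterion, the cause of intubation or adverse-event reporting. All of this stands, and it confines the point to shorter or milder episodes. The protocol does not relate RASS to the coma score, so how much those records would catch cannot be calculated.

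A second reply is that summaries can be settled in a SAP and that nonparametric tests are already allowed. This stands only in part. The daily mean is a rule for what is copied from the chart, and neither a SAP nor a rank test can recover a lowest value from a mean. Someone would have to return to the ICU charts, which is possible because the readings remain there.

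A reader might also infer more than the text supports:
- *That -1 to 0 is the target during treatment, or that such means will be reported as on target.* The protocol sets this level at the baseline assessment only.
- *That the trial claims better alertness than systemic sedation.* The introduction reports maintained alertness in a feasibility study, without that comparison, and the aim does not name alertness.
- *That VAS pain has the same fault and needs a daily maximum.* VAS is not signed, so cancellation cannot occur, and nothing checked here argues for that change.

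**Conclusion.** The concern holds in a limited form. The rule for collecting RASS discards information on over-sedation that is already charted. With no reading above 0, an in-band mean can conceal up to two of six readings at -3 or lower, or one at -4 or lower; positive readings raise these limits. This rests on six readings a day and on the assumed integer scale, though the two simplest examples need only that scores of -3 and -4 exist.

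It would be too strong to say that deep sedation goes unseen. It stays in the ICU chart, and its severe consequences are recorded elsewhere. What is missing is a trial variable that shows short or moderate troughs by arm. RASS is one of many secondary comparisons, and no primary result, sample size or error rate depends on it. This is an improvement worth making, not a flaw that threatens the trial.

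**What to change.** Keep the daily mean. From the same four-hourly charts, also record for each patient-day the lowest RASS, the number of the six readings below -1, and the number above 0, with the two counts kept separate. State in the outcome list that these are compared between arms alongside the mean.

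The cost is three short entries per patient-day. If RASS is collected over the full 120 hours of observation in all 50 recruited patients, that is at most 50 × 5 × 3 = 750 entries. Nothing new is measured and care at the bedside does not change.

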**NIV weanability**

Once a day, daily data will be collected as- weaned fully from NIV/ weaning from NIV ongoing/ same as yesterday/ not wean-able/ respiratory support increased/intubated)

Hours off NIV will be recorded as – 0/ <12/ 12-18/ >18 and off NIV

**Respiratory patient-discomfort and dyspnea**

Discomfort- Unmarked 100 mm visual analogic scale from "no discomfort" to "maximal imaginable discomfort,"

Dyspnea- Likert scale model indicating marked improvement (+2), slight improvement (+1), no change (0), slight deterioration (-1) and marked deterioration (-2).

**Intubation and mortality rates,**

Duration of NIV and invasive mechanical ventilation

Cause for conversion to IMV- Progressive respiratory failure/ New Sepsis/ Neurologic dysfunction/ Hemodynamic instability

The length of ICU-stay,

The organ dysfunctions and adverse events, including cardiac dysrhythmia, septic shock, and cardiac arrest, will be recorded until the ICU stay.

Mortality will be followed today 28.

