**Safety monitoring and adverse events**

Data and safety monitoring- Adverse effects will be documented and reported to the IEC.

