**EPIDURAL**

Baseline PT/ INR and platelet levels should be within an acceptable range to allow epidural insertion. Insertion catheter between 9 to 2 pm on the given day per the protocolized LMWH given at 7 pm on the units: or at least 4 hrs before the next dose of UFH and 12 hours after the last dose.

**Remove** the **catheter** a minimum of 4 -6 hours after a dose of UFH. Administer the next dose of UFH no sooner than 2 hours after **catheter removal**. Once-daily low-molecular-weight heparin (LMWH).

Daily site inspection (antimicrobial incise drapes transparent dressing) is done each time the drug/ sham injection is made. The injection port is kept well covered and sealed and brought to the side near the flank/ shoulder. The epidural catheters (True or Sham) will be in situ for a minimum of 2 doses or 48 hours, whichever is more, and a maximum of 4days (96 hours of catheter and 120 hours of observation).

All asepsis will be maintained for the control group as in the Intervention group, a Local injection anesthetic will be given at the L2-L3/ L3-L4 site, and the catheter will be taped tightly to the skin and dressing done to match the intervention group.

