**Respiratory Drive and related parameters**

Once at baseline and once every 8 hours after that, the following will be assessed till the epidural catheter is in situ, or five days whichever is greater.

The researcher will do the baseline assessment, be aware of the group allocation, and insert the epidural catheter (true or sham). She/ He will mark the site of best visualization for USG probe, ensure best fit NIV interface and assess baseline subjective comfort scores.

After that, all assessments will be done by a fixed set of postgraduate ICU trainees, all trained in TFDi assessment but blinded to group allocation.

Ultrasound-guided TFDi- This procedure will be performed as described earlier.(17,19)

The patient will be supine with head-end elevated to 30 %. The right hand will be abducted and kept near the head. The diaphragm will be located by placing the transducer in the intercostal space above the right 8^th^- 11^th^ intercostal space, in the anterior- axillary line, directing the ultrasound beam perpendicular to the diaphragm. The inferior border of the costophrenic sinus will be identified at end-inspiration as the zone of transition from the lung sliding shadow to the visualization of the diaphragm and liver. The zone of apposition will be noted.

The diaphragm thickness will be recorded in time motion (TM) mode.

The sweep speed will be adjusted to obtain a minimum of three to 8 cycles on the same image.

Several diaphragm images (outlined by the two clear, bright parallel lines of the pleural and peritoneal membranes) will be located: the image will be discarded if the two bright lines are not visible. The least and maximum thickness as on eyeballing will be located and a picture stored for subsequent quantitative analysis and crosschecking by a blinded assessor.

The position of the first (baseline) USG assessment will be marked on the skin to allow all subsequent recordings from the same position.

A note will be made of the ongoing sedation dosages and ventilator settings during the measurement of TFdi (settings will be kept the minimum required for patient comfort – but will not be changed/ dictated for purposes of the study)

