**Sample size**

Sample size justification A pilot study showed the mean TFDi in COVID 19 patients on PEEP 5 and clinically optimal pressure support to be 45% (SD 15); To decrease this by 30% at 36 hours after the dose of morphine with allocation in a 1:1 ratio, 21 patients will be needed in each group.

Compliance and missing data- All analyses will be based on the groups as randomly allocated: an intention-to-treat analysis. A per-protocol analysis will also be done. The statistical significance will be taken as the 5% level for the top comparisons and the subsidiary comparisons, the 1% level. Patients with a P/F ratio > 150 at inclusion will be compared to those with lower values.

Data Storage- Because of the unique challenges of repeated data capture in COVID ICU, all repetitive data will be captured photographically and sent to a central data repository online to be categorized and stored by patient name and time of data capture (once every 8 hours), making in 14-time points of data capture for each patient. Data storage will be by blinded personnel.

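### Adverse-event recording ends with the ICU stay, so observation time can differ between arms and complications after ICU discharge have no defined collection period

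*Protocol*

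**What the plan says.** **Adverse events.** The section *Intubation and mortality rates* has organ dysfunctions and adverse events, "including cardiac dysrhythmia, septic shock, and cardiac arrest, will be recorded until the ICU stay". The same section follows mortality to day 28. *The interventions* follows patients to death or 28 days after ICU discharge. *Post-recruitment retention strategies* follows them for the hospital stay or 28 days, whichever is longer. *Safety monitoring and adverse events* adds, without a time limit: "Adverse effects will be documented and reported to the IEC".

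**Catheter complications.** *Outcome assessment* commits to recording "catheter pullouts, and complications such as bleeding/ infection/ hematoma will be documented", again with no time limit. *Epidural Catheter* describes its item as "Ease of insertion and complications during catheter insertion and removal", although its list also contains accidental removal and blockage. *EPIDURAL* provides daily site inspection, tied to each drug or sham injection.

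**ICU stay as an outcome.** Length of ICU stay is among the objectives in *The research question*, is an outcome measure in *Outcome assessment*, and is a secondary comparison under *Statistical analysis*.

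**Repeated readings.** *Respiratory Drive and related parameters* requires a baseline assessment and then 8-hourly assessments "till the epidural catheter is in situ, or five days whichever is greater". *EPIDURAL* gives "a maximum of 4days (96 hours of catheter and 120 hours of observation". The Data Storage paragraph of the second *Sample size* section describes 8-hourly capture, "making in 14-time points of data capture for each patient".

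**The concern.** A safety record whose length is set by ICU stay ends at a moment that treatment may move. If morphine shortens the stay, its arm is watched for less time and can show fewer events without being safer. If it lengthens the stay, the reverse holds. The events named (dysrhythmia, septic shock, cardiac arrest) and organ dysfunctions can accrue over the whole illness, so time at risk matters.

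The limit also leaves a gap. A patient can leave the ICU, remain in follow-up, and have an event that no section says will be collected. For the catheter this matters by arm: only the intervention group's catheter enters the epidural space, so a late epidural infection or haematoma that goes uncollected would flatter the intervention. Site inspection does not close the gap, because it is tied to injections and ends with the last one.

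The count of 14 time points is a different matter. It concerns how far the repeated diaphragm thickening (TFdi), ventilator and comfort record extends, not safety.

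**Working it through.** **A. Adverse-event window**

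The protocol gives no expected ICU stay and no event rate, so there is no figure to reproduce. The check is to set the end points side by side.

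| Item | Recording ends |
|---|---|
| Organ dysfunctions, adverse events | End of ICU stay |
| Adverse effects reported to the ethics committee | Not stated |
| Catheter bleeding, infection, haematoma, pullouts | Not stated |
| Site inspection | Last injection |
| Mortality | Day 28 |
| Patient follow-up | Death or 28 days after ICU discharge; elsewhere, hospital stay or 28 days, whichever is longer |

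A haematoma or infection after catheter removal but before ICU discharge falls inside the adverse-event window. After ICU discharge, no section defines a collection period.

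*Illustration of size.* Assume the same constant daily hazard h in both arms and mean ICU stays L1 and L2.

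- Expected events per patient = h × L, so the ratio between arms is L2/L1, whatever h is.
- Equal stays: ratio 1.
- Assumed stays of 8 and 12 days: 12/8 = 1.5. With the arms reversed, 8/12 = 0.67.
- For the proportion with at least one event, treating the stays as fixed at 8 and 12 days, the ratio is (1 − exp(−12h)) / (1 − exp(−8h)). At an assumed h of 0.02 per day this is 0.213/0.148 = 1.44. At 0.05 per day it is 0.451/0.330 = 1.37.

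The stays and hazards are assumptions, not protocol figures. They show the mechanism and do not predict this trial's result.

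**B. Number of time points**

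Inputs: interval 8 hours; duration 96 hours (catheter) or 120 hours (observation, five days); stated count 14. Points = hours/8, plus 1 if baseline is counted.

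| Duration | Without baseline | With baseline |
|---|---|---|
| 96 h | 96/8 = 12 | 13 |
| 120 h | 120/8 = 15 | 16 |

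Neither duration gives 14. Working backwards:

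- If baseline is one of the 14, the last reading is at 13 × 8 = 104 h, which is 16 h short of 120 h.
- If all 14 follow baseline, the last is at 14 × 8 = 112 h, which is 8 h short.

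For a catheter removed at 96 h, full capture gives three later readings (104, 112 and 120 h). Fourteen points give one or two. The planned 24-hourly TFdi comparison at 120 h would have no reading under either count.

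**The case against.** **Catheter complications are better covered than one section suggests.** A reader of *Epidural Catheter* alone might infer that complications are recorded only at insertion and removal. The documents do not support that. *Outcome assessment* says that "complications such as bleeding/ infection/ hematoma will be documented", with no time limit. Inspection is daily while injections continue, the *Epidural Catheter* list includes in-situ events, and the general adverse-event item covers the rest of the ICU stay. Its list of events opens with a word of inclusion and is not exhaustive. This objection stands. What remains is narrower: no defined period after ICU discharge, and no check specified once injections stop.

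**The ICU limit may be a reasonable choice.** The catheter is in place for at most 96 hours and observation runs to 120 hours, so immediate drug effects should mostly fall within the ICU stay. *Statistical analysis* does not name adverse events among the secondary comparisons, and an unseen analysis plan may handle exposure time. This stands in part. It lowers the concern for immediate effects. It does not help with organ dysfunction, septic shock or late catheter events, and an analysis plan cannot recover events that were never collected.

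**The 1.5 factor is hypothetical.** It is. It supports the direction of the problem, not its size.

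**The 14 points say nothing about safety.** A reader might infer that the safety window is also short in hours. *Data collection and management* shows that the photographed data are ventilator readings, diaphragm ultrasound, and comfort and dyspnoea scores. Excessive respiratory depression is defined from blood gases taken at least daily. The sample size targets 36 hours, well inside any reading of the count. The mismatch is therefore only a data-schedule inconsistency.

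**Conclusion.** The point holds in a limited form. The protocol fixes an adverse-event window that ends with ICU stay, an outcome that treatment may change, while follow-up continues to 28 days or longer. Observation time can differ between arms, and events after ICU discharge, including late catheter infection or haematoma, have no defined collection period. The general statement on reporting adverse effects sets no window and does not repair the explicit limit.

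The size of any bias is unknown. It is nil if ICU stays are equal and hazards match; a count ratio of 1.5 needs the assumed stays of 8 and 12 days and a constant hazard. The documents do not show that late complications would necessarily be lost, only that nothing secures their collection.

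Separately, 14 time points contradicts the five-day, 120-hour schedule, falling short by 16 or 8 hours depending on whether baseline is counted. This affects the tail of the TFdi record, not the safety data. The change is worth making because it is cheap and the missing events cannot be recovered afterwards.

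**What to change.** 1. Replace the ICU-stay limit with one fixed window from randomisation for every patient, for example to day 28 or death, covering organ dysfunctions and adverse events both in the ICU and after it.
2. Apply the same window, in both arms, to catheter-related bleeding, infection and haematoma, and bring *Outcome assessment*, *Epidural Catheter* and *Intubation and mortality rates* into line with it.
3. Compare arms on that window, with deaths shown alongside. State randomisation as the single origin for day 28, since the follow-up statements now differ.
4. Separately, reconcile the 14 in the Data Storage paragraph with *Respiratory Drive and related parameters*, so that the TFdi record reaches 120 h: 16 points with baseline, or 15 after it.

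**Cost.** Case report form wording, one number, and some adverse-event data collection on the ward or after discharge. Follow-up is already planned, but the protocol describes no contact at which complications are asked about, so those questions must be added. No treatment rule changes.
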